### Primary and secondary outcomes

The primary outcome was the change in systolic BP at 6 months. Secondary outcomes included change in diastolic BP, the proportion of participants with adequate BP control at 6 and 18 months, and the effect of treatment on behavior change (i.e., weight loss, dietary pattern, physical activity) at 6 and 18 months. The 6-month outcomes correspond to the maximum impact of the patient intervention but may be too early to reflect maximum impact of the MD intervention. The 18-month outcomes assess the durability of the patient intervention and the cumulative (perhaps maximal) effect of the MD intervention.

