### Analysis plan

The data cleaning and analysis stage of the HIP trial has begun. The adequacy of randomization will be assessed by comparing the baseline characteristics of the 4 study groups. Chi-square tests will be used for categorical variables, and the analysis of variance will be used for continuous variables.

For the patient intervention groups only, various measures pertaining to adherence to the patient intervention and its impact on intermediate outcomes will be summarized. For example, for each cohort, the number of intervention sessions attended will be summarized. Similarly, changes in weight, diet, and exercise will be tabulated, and whether the mean changes equal zero will be determined.

For the main analysis of BP changes, results by group and cohort will first be summarized, and then tested for a cohort-by-group interaction. If this interaction is non-significant–suggesting that the intervention effects are similar across cohorts–summary results will be reported but will include cohort as a control variable in all models. For the continuous outcome of systolic BP, the main comparison will be derived from an analysis of covariance model that controls for cohort and baseline systolic BP. The primary hypotheses of interest will be the main effect of the patient intervention, the main effect of the physician intervention, and the patient-by-physician interaction. This last interaction assesses, for example, whether the patient and physician interventions have a separate impact on outcome or, alternatively, whether they act synergistically. For the categorical outcome of percentage of patients at goal, a similar strategy will be followed using logistic regression, and these analyses will also be stratified by whether the patient was at goal at baseline.

The analysis plan accounts for the correlations among the responses for individual patients, these correlations being induced by the nesting of time points within patients within physicians within practices. The analysis of variance paradigm will be used, accounting for the correlations among the 3 time points by separately analyzing the paired scores representing differences between baseline and 6 months and between baseline and 18 months. These comparisons can be preceded by a statistical test, such as Hotelling's T^2^, that takes explicit account of these correlations.

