### Sample size and statistical power

The power calculations assumed that the impact of accounting for covariates such as baseline blood pressure (which increases statistical power) and the impact of the clustering inherent to this design (which decreases statistical power) would approximately offset and, thus, that power calculations from the 1-way analysis of variance would apply. If so, having approximately 340 patients complete the study would yield approximately 80% power to detect main effects, although the power to detect an interaction between the physician intervention and patient intervention would be smaller. After accounting for expected drop-outs, the minimum sample size for the primary analysis was set at 400.

Preliminary planning also considered 2 other factors, both of which supported an increase in the sample size above 400, if feasible. First, it was anticipated that the study would analyze various secondary outcome variables, some of which might have effect sizes that were less than 0.3. Second, so that the results could be as generalizable as possible, the study strove to include as many clinics as possible. The design originally intended to include 5 sets of clinics, a number which was also suggested by the fact that the most conservative statistical analysis of the impact of the physician intervention–namely, a sign test that simply counts which clinic out of each pair had the better outcome–would be statistically significant if the physician intervention outperformed the controls at each pair of clinics.

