The patient intervention required weekly attendance at group sessions that lasted up to 2 hours. Several of the clinics served rural areas requiring significant travel by the participants. Some communities were not accustomed to the research activities of AMCs and, thus, patients in those areas may have been less inclined to join a research study for reasons related to lack of trust or information. While these factors mimic challenges to implementation of the patient intervention in real-world settings, they created a greater challenge for recruitment into a research study, especially given that recruitment was based on blind mailings. The initial recruitment letter asked potential participants to call the study team only if they were not interested in participating (an opt-out strategy); if the study team did not receive a response, then a follow-up call was made to answer any questions and determine interest in participating. However, the ratio of calls to enrollees was low, so the recruitment letter was changed to allow patients to also opt in. This option allowed participants to self-select for inclusion, which may have selected more motivated individuals but is still likely to generalize to a real-world implementation of the study intervention, which would ultimately require voluntary participation.

Recruitment of CHAs was somewhat challenging. The initial goal in enlisting CHAs was to recruit people with "natural helper" personalities from the same communities as the target patient population. To that end, flyers were posted in participating clinics, and clinic staffs and community leaders were asked to suggest people from within their communities. The response to this recruitment effort was relatively modest. Although we were able to recruit an adequate number of CHAs for the study with a minimal budget, our selection pool was limited. Future studies incorporating the CHA element may consider including a budget for a greater advertisement effort and other strategies to enhance recruitment.

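### Analysing the 6-month and 18-month blood pressure changes separately leaves the 18-month result needlessly exposed to selective loss after month 6

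*Protocol article*

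**What the plan says.** Under Analysis plan, the article says the correlations among the three time points are handled by "separately analyzing the paired scores representing differences between baseline and 6 months and between baseline and 18 months". For systolic pressure, "the main comparison will be derived from an analysis of covariance model that controls for cohort and baseline systolic BP". The only joint device is optional and is a test, not an estimator: "These comparisons can be preceded by a statistical test, such as Hotelling's T^2^, that takes explicit account of these correlations".

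Under Primary and secondary outcomes, the primary endpoint is systolic change at 6 months. The later visit has its own role: "The 18-month outcomes assess the durability of the patient intervention and the cumulative (perhaps maximal) effect of the MD intervention".

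Under Sample size and statistical power, "having approximately 340 patients complete the study would yield approximately 80% power to detect main effects", and then "After accounting for expected drop-outs, the minimum sample size for the primary analysis was set at 400". The article gives no rule for missing blood pressure values and no drop-out rate by arm.

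**The concern.** A difference score exists only for a patient who has both the baseline and that follow-up value. Analysing each difference on its own therefore gives up the link between the 6-month and 18-month readings. For a patient who leaves after month 6, the observed 6-month pressure is the best available information on what the 18-month pressure would have been, and the stated 18-month analysis does not use it. Conversely, a patient seen at baseline and 18 months but not at 6 months is absent from the 6-month analysis. In its standard form the Hotelling test needs both differences, so it would run on a third, smaller set.

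What is at stake is how the 18-month result is read. If intervention patients who respond poorly leave more readily than comparable controls, those who stay look better than the arm as a whole, and attrition can pass for durability. The article gives some reason to think that motives for staying differ by arm after month 6: the intervention arm receives monthly advisor calls, while controls are offered a shortened programme only after the final 18-month visit.

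**Working it through.** **The plan's own figures.** The documents imply a standardised effect of 0.3. Two-sided 5% significance is assumed, as it is not stated.
- Power with 170 per arm = Φ(0.3·√(170/2) − 1.96) = Φ(0.806) = 0.79. The stated 80% is reproduced.
- 1 − 340/400 = 0.15, so about 15% loss was allowed for.
- 574 were enrolled. With 15% lost, 574 × 0.85 ≈ 488 remain, about 244 per arm. Power = Φ(0.3·√(244/2) − 1.96) = Φ(1.354) ≈ 0.91, before any clustering penalty.

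Power is therefore not the issue. The issue is who is analysed at 18 months.

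**Inputs for the size of bias.** All are assumptions except the arm size, which is 574/2 = 287. SBP has SD 14 mmHg at each visit, with correlation 0.5 between any two visits. The true effect is −4 mmHg at 6 and 18 months. Loss after month 6 is 15% or 25%. The log-odds of loss rise by k per SD of 6-month change (a worse response makes loss more likely).

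**Approximate formula**, for an 18-month analysis of covariance in those who stay:
- Covariance of 6- and 18-month SBP given baseline = 0.5·14² − 0.5²·14² = 98 − 49 = 49.
- SD of the 6-month change = 14·√(2·(1 − 0.5)) = 14.
- An arm with loss p and slope k has its 18-month mean among stayers shifted by about −(49/14)·k·p = −3.5·k·p.
- The bias in the treatment difference is the intervention shift minus the control shift. It vanishes when k = 0 in both arms, or when k and p are the same in both.

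**Simulation check**, 3,000 trials per row. The joint estimate also uses the 6-month value.

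| Loss | k control / intervention | Formula bias | Separate 18-month estimate (SE) | Joint estimate (SE) |
|---|---|---|---|---|
| 15% | 0 / 0 | 0 | −3.93 (1.10) | −3.93 (1.10) |
| 15% | 0 / 0.5 | −0.26 | −4.26 (1.09) | −4.00 (1.08) |
| 15% | 0 / 1.0 | −0.53 | −4.45 (1.12) | −3.98 (1.11) |
| 15% | 0.5 / 0.5 | 0 | −3.98 (1.12) | −3.99 (1.10) |
| 25% | 0 / 0.5 | −0.44 | −4.44 (1.17) | −4.02 (1.17) |
| 25% | 0 / 1.0 | −0.88 | −4.75 (1.17) | −4.00 (1.15) |
| 25% | 1.0 / 1.0 | 0 | −3.97 (1.16) | −3.98 (1.15) |

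Across repeated runs of these settings the excess was 0.2 to 0.8 mmHg, that is 5% to 20% of the assumed 4 mmHg.

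**A harsher variant.** Use change scores without baseline adjustment, with SD 13, correlation 0.5 between the two changes, a true 18-month difference of −3, and loss of 15% in control and 16–19% in intervention. The separate estimate is then −3.5 to −4.1, an excess of 0.5 to 1.1 mmHg. At the highest loss its standard error is 13·√(1/244 + 1/233) ≈ 1.19, so this too stays below one standard error. The plan adjusts for baseline, so the table is the closer guide.

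**The case against.** The strongest reply is that the article states how correlation is handled and says nothing about missing data. Separate analyses of covariance are compatible with multiple imputation, and an article may leave that to the full plan. This stands, and the point is limited accordingly: it describes the stated method when nothing is imputed.

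A reader might take the sample size section as proof of a completers-only analysis. It is not. Inflating for drop-out is routine under any method, and the text sets 400, not 340, as the minimum for the primary analysis.

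A reader might also blame selective loss on session burden, since "The patient intervention required weekly attendance at group sessions that lasted up to 2 hours" (Discussion). Those sessions fall in the first 6 months, and from month 6 to 18 the intervention is a monthly phone call. Session burden would mainly cause loss before month 6, and a joint model cannot recover a patient with no follow-up reading at all.

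It is likewise too strong to say that the primary result is compromised, or that the article plans a formal comparison of 18 with 6 months. Patients lost after month 6 still count in the 6-month analysis, and the text says only "The 18-month outcomes assess the durability of the patient intervention". Finally, the joint estimate recovers the truth in the table because loss was generated from the observed 6-month value, which is exactly what such a model assumes.

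What survives is that the stated method discards information already collected, at the visit where loss is likely to matter most.

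**Conclusion.** The point holds as a recommended improvement to the 18-month analysis, not as an error that undermines the trial. As stated and without imputation, the 6- and 18-month effects can rest on different patients, and the 18-month effect ignores the 6-month pressure of those lost later. The same applies to the physician effect at 18 months, which the article regards as perhaps its maximum.

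The bias appears only if the link between loss and response differs by arm. Under the assumed values it is about 0.2–0.8 mmHg against a standard error of about 1.1–1.2. It is nil if loss is unrelated to response or equally related in both arms. With no arm-specific loss reported, its true size and even its presence are unknown. The 6-month primary result is little affected: it loses only patients without a 6-month reading.

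**What to change.** Estimate systolic and diastolic pressure at 6 and 18 months from one likelihood-based repeated-measures model that includes every randomised patient with any follow-up reading. Include:
- visit-specific patient, physician and patient-by-physician effects, since the interaction is one of the three primary hypotheses;
- visit-specific baseline pressure, and cohort;
- an unstructured within-patient covariance;
- the nesting of patients within physicians within practices that the Analysis plan already recognises.

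Take the 18-month effects and an explicit 18-versus-6-month durability contrast from this model, and drop the optional Hotelling test. Keep the pre-stated 6-month analysis of covariance and report the model's 6-month contrast beside it. Analysis has begun and the study statistician was not blinded to interim results, so replacing the primary estimator now would invite the charge of a data-driven choice. Report missingness by visit in each of the four cells.

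The cost is modest extra programming and no new data. In the simulations above, precision was essentially unchanged. The model still assumes that missingness depends on observed values, and it does not recover patients lost before any follow-up reading.

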### Sample size and statistical power

The power calculations assumed that the impact of accounting for covariates such as baseline blood pressure (which increases statistical power) and the impact of the clustering inherent to this design (which decreases statistical power) would approximately offset and, thus, that power calculations from the 1-way analysis of variance would apply. If so, having approximately 340 patients complete the study would yield approximately 80% power to detect main effects, although the power to detect an interaction between the physician intervention and patient intervention would be smaller. After accounting for expected drop-outs, the minimum sample size for the primary analysis was set at 400.

Preliminary planning also considered 2 other factors, both of which supported an increase in the sample size above 400, if feasible. First, it was anticipated that the study would analyze various secondary outcome variables, some of which might have effect sizes that were less than 0.3. Second, so that the results could be as generalizable as possible, the study strove to include as many clinics as possible. The design originally intended to include 5 sets of clinics, a number which was also suggested by the fact that the most conservative statistical analysis of the impact of the physician intervention–namely, a sign test that simply counts which clinic out of each pair had the better outcome–would be statistically significant if the physician intervention outperformed the controls at each pair of clinics.

Near the conclusion of the 6-month follow-up for Cohort 3, the Data Safety Monitoring Board (DSMB) reviewed the study design–in particular, whether it would, in view of the trial's limited budget, be appropriate to reduce the number of cohorts from 5 to 4. This DSMB review included a comparison of the results of the study to date (to which the investigators, with the exception of the study statistician, were blinded) with the assumptions of the power calculations. In approximate numbers, instead of 40% of patients maintaining BP control at baseline, the figure was actually 70%. Moreover, over 95% of the patients who were in BP control at baseline were also in control at 6 months, raising the possibility that using a dichotomous BP control variable as the primary outcome would suffer from a ceiling effect. (Note that such a ceiling effect was not necessarily certain; for example, an effect size of 0.3 could still be generated from a pattern of outcomes centered around 70%, but this preliminary analysis did suggest that patients who were in BP control at baseline were likely to provide less information than desired toward distinguishing the impacts of the interventions.)

In light of these considerations, the DSMB recommended: (a) to reduce the number of cohorts to 4 (to conserve budget); (b) to focus recruitment in Cohort 4 on patients who were not in BP control at baseline (to ensure that the study population approximated the original target population as much as possible); and (c) to change the primary outcome to change in SBP, measured as a continuous variable, while maintaining the dichotomous measure of BP control as a secondary outcome (to increase statistical power by, for example, being able to differentiate between greater decreases in SBP among patients who were in BP control at baseline).

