### Enrollment and randomization of MDs

To avoid contamination among physicians in the same practice, randomization occurred at the level of the practice. Four matched pairs of primary care practices were randomly assigned to physician intervention or control. Practices were matched according to specialty (internal medicine or family practice) and participant mix (percent of participants with Medicaid or Medicare without supplemental insurance). Within each practice, all physicians were invited to participate, with a goal of enrolling 4 physicians at each clinic. All physicians at a given clinic were assigned to the same intervention.

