### Enrollment and randomization of patients

After enrolling clinics and physicians, participants were then recruited from the patients of the enrolled physicians. Ten to 15 patients cared for by each participating MD were enrolled and randomized to the behavioral intervention or usual care.

Billing codes were used to identify hypertensive patients. Each participating physician reviewed the list and removed names of patients considered unsuitable candidates for study participation. Recruitment letters were mailed on practice letterhead with the physician's name on the signature line. Patients were asked to call the research coordinator within 10 working days to decline participation in the study. After the 10 days, a member from the study staff called unresponsive patients to assess their willingness and eligibility to participate (Table 1).

**Table 1 T1:** HIP eligibility criteria

**Inclusion criteria**	• Receiving primary care from a randomized physician
	• Diagnosis of hypertension: Average SBP ≥ 140 mm Hg and/or DBP ≥ 90 mm Hg on at least 2 clinic visits in the past 12 months or taking antihypertensive medication
	• Age 25 years or older at the time of the initial screening visit
	• Willing and able to participate fully in all aspects of the intervention
**Exclusion criteria**	• Cardiovascular event within the past 6 months (if more remote history, eligible with MD approval)
	• Chronic kidney disease (estimated GFR < 60 ml/min)
	• Planning to leave the area prior to the anticipated end of participation
	• Pregnant, breast feeding, or planning pregnancy prior to the end of participation
	• Current participation in another clinical trial
	• Investigator discretion for safety or adherence reasons
	• Household member of another HIP participant or of an HIP staff member

DBP = diastolic blood pressure; GFR = glomerular filtration rate; HIP = Hypertension Improvement Project; MD = physician; SBP = systolic blood pressure.

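### The single 80% power figure for main effects holds for the patient intervention but not for the physician intervention, which is randomized across only 8 practices

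*Protocol article*

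**What the plan says.** All references are to the protocol article. Sample size and statistical power assumes that the gain from covariates and the loss from clustering "would approximately offset and, thus, that power calculations from the 1-way analysis of variance would apply". On that condition it concludes that "having approximately 340 patients complete the study would yield approximately 80% power to detect main effects", and makes an exception only for the interaction, whose power it calls smaller. After expected drop-out the minimum sample is set at 400.

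The Analysis plan section lists three primary hypotheses: the patient main effect, the physician main effect and their interaction. The two main effects have different units of randomization. Patients are randomized individually within clinics. For the physician factor, "Four matched pairs of primary care practices were randomly assigned to physician intervention or control" (Enrollment and randomization of MDs).

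The design was first meant to have 5 sets of clinics. The monitoring board later recommended "to reduce the number of cohorts to 4 (to conserve budget"), and 8 practices took part. The article gives no power figure for the physician effect after that change.

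**The concern.** A calculation that treats 340 patients as independent tests each main effect against about 338 error degrees of freedom. That is a fair approximation for the patient factor, because intervention and control patients are compared inside the same practices. The physician factor is compared between practices, so the error term comes from 8 practice-level values. The assumed cancellation concerns the size of the standard error. It says nothing about how few practices there are to estimate that error, and a t test on 3 or 6 degrees of freedom needs a much larger ratio of effect to standard error than one on 338.

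What is at stake is interpretation. The Conclusion says that health care organizations will use the separate results to decide whether to adopt one or both interventions. A non-significant physician result, read against a stated power of 80%, would look like better evidence of ineffectiveness than the design can give.

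**Working it through.** **Inputs**
- Completers: 340. Enrolled: 574. Practices: 8 in 4 pairs (originally 5 sets, so 10). All are from the article.
- Drop-out: 340/400 = 0.85, so 15% is implied. Applied to enrolment, 574 × 0.85 = 488 completers. This is an assumption.
- Effect size: 0.3 SD. This is inferred. The article says of secondary outcomes that "some of which might have effect sizes that were less than 0.3", and uses 0.3 again when discussing the binary control outcome.
- Significance level: not stated. Two-sided 5% is inferred.
- ICC and baseline correlation: not stated. The main result does not need them.

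**Step 1. Reproduce the stated figure.** With N/2 patients per level and SD 1, the noncentrality is 0.3 × √(N/4). At N = 340 this is 0.3 × √85 = 2.766. On 338 df, two-sided 5%, power is 78.8%, which matches the stated figure of about 80%. One-sided 5% would give 87%, which does not match.

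**Step 2. Error degrees of freedom for the physician effect.** Unpaired: 8 − 2 = 6. Paired: 4 − 1 = 3. The Analysis plan section puts cohort in the models, and each of the 4 cohorts is 2 practices, so a practice-level analysis with cohort has 8 − 4 − 1 = 3.

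**Step 3. Keep the plan's noncentrality and change only the df.** This grants the assumed cancellation in full.

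| Test of a 0.3 SD effect, 340 completers | Error df | Two-sided 5% critical value | Power |
|---|---|---|---|
| Patient-level, as in the plan | 338 | 1.97 | 78.8% |
| Practice-level, 8 practices, unpaired | 6 | 2.45 | 63.8% |
| Practice-level, 8 practices, paired or with cohort | 3 | 3.18 | 47.4% |
| Practice-level, 10 practices, unpaired | 8 | | 67.9% |
| Practice-level, 10 practices, paired | 4 | | 55.4% |

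The shortfall was therefore present with 10 practices and grew with 8. For 80% power at 340 completers the physician effect would have to be about 0.37 SD (6 df) or 0.46 SD (3 df).

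**Step 4. Allow for the larger enrolment.** At 488 completers the noncentrality is 0.3 × √122 = 3.314. If the cancellation still holds, physician-effect power is 78.8% (6 df) or 60.9% (3 df). For the patient effect on 486 df it is 91%.

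**Step 5. If the cancellation does not hold.** With m = 488/8 = 61 completers per practice, baseline correlation r acting on patient-level variance only, and 4 practices per arm, the variance of the physician contrast is [ICC + (1 − ICC)(1 − r²)/m] × 4/8. With assumed values ICC = 0.02 and r = 0.5:
- [0.02 + 0.98 × 0.75/61] × 0.5 = 0.01602, so the standard error is 0.1266
- noncentrality 0.3/0.1266 = 2.37
- power 51% (6 df) or 38% (3 df)

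Under the same formula, ICC 0.01 gives 66% or 50%, and ICC 0.05 gives 30% or 23%. These depend on the assumed ICC and r, which the article does not supply.

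**The case against.** The strongest reply is that the article does not claim 80% unconditionally. It makes the figure depend on covariates and clustering cancelling, says that clustering costs power, discusses a clinic-pair sign test as the most conservative physician analysis, and warns under Primary and secondary outcomes that 6 months may be too early for the full physician effect. All of that is true and softens the point. It does not remove it. The condition covers only the cancellation, which Step 3 grants, and nothing in the text mentions the few practice-level degrees of freedom. The sign test does not help after the cut either: with 4 pairs its smallest one-sided p-value is (1/2)⁴ = 0.0625.

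It is also fair to say that 0.3 SD and two-sided 5% are inferred, and that the Analysis plan section fixes no error term, so 3 or 6 df is an assumption about the eventual test. This stands as a caveat, but the direction does not depend on it. A one-sided 5% test would fall from 87% to 79% (6 df) or 68% (3 df).

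Two stronger readings are not supported:
- A reader might infer that baseline adjustment can never make up for clustering. The variance formula in Step 5 shows that it can when the ICC is small. With 340/8 = 42.5 patients per practice and ICC 0.01, the total variance matches that of an unclustered, unadjusted comparison at r of about 0.65, even when r acts on patient-level variance alone.
- A reader might infer that the physician effect had at best an even chance of detection. The 6-df results of 64% at 340 completers and 79% at 488 contradict that as a general statement.

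**Conclusion.** The point holds for the physician effect. At the stated 340 completers its power is about 64% (6 df) or 47% (3 df), not 80%, with the plan's own cancellation granted. The cohort term in the planned models points to the lower value. At 488 completers the range is about 61% to 79% if the cancellation holds, and lower if it does not. The result rests on an inferred 0.3 SD, an inferred two-sided 5% level and a test that uses practice-level error. The 488-completer figures also assume 15% loss.

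The stated 80% remains reasonable for the patient effect. A reader might go further and conclude that the planned analysis is invalid or that the interaction should lose its place among the primary hypotheses. The article supports neither. It says that nesting within practices will be accounted for, and it already says that interaction power is smaller. The error lies in the power statement and in how a null physician result would be read from it.

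**What to change.** - Confine the 80% statement to the patient main effect.
- State the power for the physician main effect separately, from 8 practices and practice-level degrees of freedom. Give it as a range, and label the effect size, significance level, ICC and baseline correlation as assumptions. Say that it reflects the reduction from 5 to 4 cohorts.
- Report the physician effect by its estimate and a confidence interval on practice-level degrees of freedom, and say that a non-significant result is not evidence of no effect.

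This needs no more patients or practices and leaves the hypotheses unchanged. The cost is rewording and a stated power that is less favourable.
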